## **9.7 Follow up Procedures.**

Outcomes will be collected by telephone/MS TEAMS at six- and 12-weeks post-randomisation; we will also collect outcomes at six months post-randomisation if the timing of randomisation permits 6-month follow-up within the trial data collection window.

## **9.8 Modifications or discontinuation of intervention**

Should the research team/Trial Steering and Data Monitoring Committee (TSDMC) deem a need for discontinuation of the trial (e.g., for urgent safety measures), the CI will report the early discontinuation via an NRES End of Study Declaration form to the main REC with a copy to the co-Sponsors.

## **9.9 Withdrawal / dropout of participants**

Participants are free to withdraw from the trial at any point or a participant can be withdrawn by the CI/site PI. No sanctions will follow if the participant decides to leave the research at any time.

Participants who wish to withdraw will have the option of withdrawal from:

- All aspects of the trial but continued use of data collected up to that point.
- All aspects of the intervention but continued use of data collected up to that point and continue with planned completion of questionnaires and interviews as well as collection of information from routine health records for the purpose of primary and some secondary outcomes.
- Any ongoing aspects of the trial that require patient contact or completion of questionnaires, but permission to collection of information from routine health records for the purpose of primary and some secondary outcomes.

Participants can be withdrawn by the CI/site PI following:

- A change in the health status of the participant that the clinical team report justifies withdrawal (including admissions to the inpatient setting).

If withdrawal occurs, the primary reason for withdrawal (as available) will be documented in the participant's case report form (CRF). Participants who withdraw will not be replaced.

### ***9.10 End of Trial Definition***

The end of the study is the date when the last participant has completed all assessments, data queries are resolved and database locked, which is anticipated to be by month 17 from the study start.

## **10 Regulatory Approvals**

The study protocol and other relevant documentation will be submitted to, and approved by, a REC, the HRA and the appropriate local R&D departments for each site prior to entering participants into the trial.

All correspondence with the REC will be retained.

### ***10.1 Amendments***

For any amendment to the study, the Chief Investigator, in agreement with the Sponsor, will submit information to the relevant regulatory bodies for review. Substantial amendments that require review by the REC will not be implemented until that review has been completed with a favourable outcome, and other mechanisms are in place to implement at site. The Chief Investigator will work with the sites local site R&D departments as well as the study delivery team to confirm ongoing Capacity and Capability for the study.

### ***10.2 End of Study Reporting***

#### **10.2.1 End of Study Declaration**

The end of the study will be declared to the REC that gave a favourable opinion (as per the above Regulatory Approvals section) within 90 days of the study ending.

If the study is terminated early, the study will end on the date the Sponsor formally declares the study terminated in writing. The main NHS REC will be notified of early termination within 15 days of the Sponsor deciding to end the study.

### **10.2.2 End of Study Reporting**

The end of the study report will be submitted to the REC that gave a favourable opinion (as per the above Regulatory Approvals section) within 12 months of the study ending.

**Related Unexpected Serious Adverse Events (RUSAE)** - A related and unexpected SAE is an event which is related to the intervention; and 'unexpected' – that is, the type of event is not listed in the protocol as an expected occurrence.

Where AEs/SAEs occur, the team (direct care team delivering the intervention and control arms) will follow Good Clinical Practice Guidelines for the reporting to the medical team responsible for the participant's care and notify the Principal Investigator (PI). PIs at all sites will report all AEs/SAEs to the CI via the study electronic database (REDCap). The CI (unblind to allocation) will determine relatedness. The CI will then be responsible for reporting SAEs to KCL RGO.

All SAEs that are to be reported to the RGO will be signed and dated and completed by the CI. Where an RESAE occurs that does not require immediate reporting, this RESAE will be reported in the Annual Progress Report and copied to the RGO, alongside any AEs that occur that are not classified as 'serious'.

RUSAEs will be reported immediately upon knowledge of the event to the RGO and always within 24 hours. Reports of RUSAEs will be submitted to the Main NHS/ HSC REC within 15 days of the Chief Investigator becoming aware of the event, using the appropriate template. The form will be completed in typescript and signed by the Chief Investigator. The main REC will acknowledge receipt of safety reports within 30 days. A copy of the SAE notification and acknowledgement receipt will also be sent to the RGO.

In the instance of a personal data breach, the breach will be immediately reported to the CI, Sponsor's, and to the Data Protection Officer/Information Governance Department of the site that incurred the breach. The report will include full details as to the nature of the breach, an indication as to the volume of material involved, and the sensitivity of the breach (and any timeframes that apply), steps that have been taken to mitigate the risk (trying to retrieve the data asking third parties to delete information that was sent to them in error) to enable an assessment of the full risk/impact of the breach. The Sponsor will determine whether the breach meets the definition of a serious breach and warrants reporting to the regulators including the ICO <https://ico.org.uk/for-organisations/report-a-breach/personal-data-breach-assessment/>.

A joint Trial Steering and Data Monitoring Committee (TSDMC) will be informed of the number, nature and review outcomes for all serious adverse events and be asked to recommend any necessary actions.

The final report will detail the number (events and individuals) and nature of all events (AEs and SAEs) reported to members of each site and/or research team and will be submitted to the REC with the sponsor copied.

Information with regards to Safety Reporting in Non-CTIMP Research is further specified in Appendix 1.

## **11.2 Urgent Safety Measures**

A decision to implement an urgent safety measure (USM) can be made by the Sponsor, CI, PI and/or TSDMC in the event of identifying an immediate risk to participant safety. USM identified shall take immediate effect and the event will be notified to the REC no later than 3 calendar days from the date the measures are taken. Any incident identified by a site that may result in an USM must be communicated to the CI immediately via the institutional study mailbox. If the CI and the Sponsor consider the USM to affect all participants, all PIs must be informed of the USM. A protocol amendment will be submitted to the HRA and REC at the earliest opportunity (and within three days) following implementation of the USM. If the USM requires a temporary halt to the study, this will be notified by an amendment.

## **12 Data**

### **12.1 Data to be collected**

Data collection, including who the data is to be collected by, from where, the data type and the time point for collection, is outlined in Table 1. Data collection at baseline, 6 weeks post-randomisation, 12-weeks post-randomisation, and 6-months post-randomisation (if the timing of randomisation permits this follow-up within the trial data collection window) will be between the participant and a member of the research team over the telephone or MS TEAMS.

The following participant characteristics will be collected to enable baseline comparison between allocated groups: age, sex, ethnicity, Abbreviated Mental Test (AMT), Clinical Frailty Scale, living status (lives alone, with independent spouse, with dependent spouse, with family, with other), accommodation type (house/ground floor apartment with step free access, house/ground floor apartment with step access, 2nd floor or higher apartment with lift access, 2nd floor or higher with no lift access, sheltered accommodation), prefracture mobility (independent, with aid, with support of 1 person), fracture type, surgery type, length of stay (from admission to discharge from acute hospital), and any additional inpatient stay following discharge from hospital e.g. intermediate care. The acceptability, completeness, and descriptive comparison of patient reported outcome data collection will be assessed through collection of patient-reported outcome measures (via standardised tools) which satisfy the core outcome set for hip fracture trials. Additional patient-reported outcome measures (via standardised tools) which capture putative mechanisms (community mobility, falls related self-efficacy) for an effect on health-related quality of life (as the proposed primary outcome for a subsequent definitive trial) will also be collected.

Additional quantitative outcomes captured will include mortality (online death record search) and self-reported hospital readmissions (with reason which may/may not be directly related to their hip fracture surgery) as key performance indicators of care after hip fracture surgery; resource use using a bespoke data collection form to assess feasibility of collecting health economic data while

minimising the burden on participants; exercise adherence during intervention delivery for the intervention arm, and participant and therapist acceptability with the use of a brief validated questionnaire at the end of the trial. For those in the intervention arm, we will capture whether participants engaged family/friends (yes/no).

For patients who do not speak English, patient-reported outcome measures which have an established translated, validated, and (where applicable) culturally adapted version in the appropriate language will be circulated by post to the participant with a pre-paid envelope for return. Patient characteristics and additional quantitative outcomes will be collected using local interpreting services.

To assess fidelity for the intervention group, we will audio record intervention sessions between each participant and their supporting physiotherapist/occupational therapist/therapy assistant including discussion of questions/responses recorded in participant diaries (which are to be completed to capture unsupervised outdoor mobility training between visits). The audio recording will enable assessment of the five intervention fidelity domains (design, training, delivery, receipt, and enactment) identified by the National Institute of Health Behaviour Change Consortium. Fidelity assessment will be supplemented by study-specific questionnaires completed by the physiotherapist/occupational therapist/therapy assistant after each supervised session for both intervention and usual care groups.

Qualitative data on perceived barriers and facilitators to intervention delivery will be captured through purposively sampled (site, pre-fracture mobility, living status, accommodation type, sampled by the research team) remote (telephone/MS TEAMS) semi-structured interviews between a member of the research team and participants (until data saturation is reached). Therapists will contribute their perspectives on barriers and facilitators to intervention delivery in four 60-minute online focus groups via MS TEAMS facilitated by the research team. We will target recruitment of at least 80% of the therapists involved in intervention delivery at each site in each focus group. We will also extend invitations for interviews between a member of the research team and people at higher organisational levels (e.g., local allied health professional community team leaders and service managers) for their perspectives on potential barriers and facilitators.

Data collection forms (including topic guides) are detailed in additional files.

## ***12.2 Data handling and record keeping***

Data will be handled in adherence to the UK General Data Protection Regulation and Data Protection Act 2018.

### **12.2.1 Electronic database**

Quantitative data, including participant demographics, will be entered into electronic case report forms (eCRFs) and managed in an instance of REDCap, an Electronic Data Capture system developed by Vanderbilt University. REDCap will be hosted securely within University of Exeter's Amazon Web Services (AWS) account. Data will be securely stored in AWS data centres in the UK with access

limited to only authorised staff. The REDCap database will be encrypted at rest. Access to REDCap public facing website via web browser will be encrypted using the appropriate Transport Layer Security (TLS) protocol.

Study projects and eCRFs will be built and validated in REDCap a priori to appropriate standards by ExeCTU in collaboration with the research team. Data collected in REDCap will be pseudo-anonymised with the use of the patient identification number as the primary identifier of the participant for data entered to REDCap. The eCRFs will be programmed to generate notifications for possible data entry errors (e.g. range checks) and missing key data points. Password protected user entry will be limited to therapists and members of the research team who need to enter or analyse data. Patient contact details will be available to 1) site therapists to arrange intervention delivery; and 2) authorized members of the research team who are required to contact participants for data collection/interviews/to send study findings at the end of the trial.

After completion of the trial, quantitative data will be transferred from Exeter CTU via a secure file sharing platform to KCL where it will be stored for 5 years after which it will be destroyed in line with KCL policies on data destruction. Following publication of the primary paper, anonymised electronic REDCap data will be exported and stored alongside anonymised transcriptions of interviews indefinitely on the King's Open Research Data System (<https://www.kcl.ac.uk/researchsupport/managing/preserve>), with proof of ethical approval as a condition of access.

### **12.2.2 Paper-based data**

Paper-based identification, screening and enrolment logs, and consent forms, will be completed by therapists at participating sites. Paper-based study specific questionnaires will be completed by therapists delivering the intervention and comparator in the community. All paper-based data will be stored in a locked cabinet/drawer within a secure room at the participating site. Therapists will be required to enter all paper-based quantitative data to electronic CRFs on the REDCap Cloud database (see 13.2.1). Paper-based data (including consent forms) will be stored for 5 years after which they will be destroyed in line with local Trust policies on data destruction. For patients who do not speak English, pseudo-anonymised patient-reported outcome measures returned by post will be stored in a locked cabinet in a restricted access room and building at KCL for 5 years after which they will be destroyed in line with KCL policies on data destruction.

### **12.2.3 Qualitative data**

For intervention group participants, all supervised treatment sessions will be audio-recorded to enable a direct assessment of treatment fidelity (primary objective). These audio-recordings will be uploaded by the therapist to a secure KCL SharePoint server accessible only to the research team, labeled with the participant identification number after which the recording will be deleted from the audio recording device.

For a sample of participants, the research team will audio-record semi-structured interviews completed at the end of their time in the trial. The research team will also audio-record semi-structured interviews with local allied health professional community team leaders and service

managers completed by MS TEAMS and focus groups with therapists via MS TEAMS. These audio-recordings will be uploaded by the research team to a secure KCL SharePoint server accessible only to the research team, pseudo-anonymised with the participant identification number/file identification number (for leaders, managers and focus groups) after which the recording will be deleted from the audio recording device. These recordings will be transcribed verbatim and anonymised after which the audio-files will be permanently deleted.

Following publication of the primary paper, anonymised transcriptions of interviews will be stored on the King's Open Research Data System indefinitely (<https://www.kcl.ac.uk/researchsupport/managing/preserve>), with proof of ethical approval as a condition of access.

### ***12.3 Access to the dataset***

Access to REDCap will be limited to site investigators and members of the research team who require access to enable intervention delivery and/or data entry, and to the Sponsor for monitoring and auditing purposes. The database will also be accessible to dedicated members of ExeCTU responsible for database management, export, and/or analysis. Access rights will be managed by specific role based access, ensuring staff can only perform functions within REDCap according to their role.

Access to qualitative data will be limited to members of the research team who require access for analysis and to the Sponsor for monitoring and auditing purposes. Further, access to audio-recordings of interviews and focus groups will be granted to an external transcription service 'The Typing Works' who will retain access only for as long as required to transcribe the recordings, after which access will be revoked. A service level agreement will be put in place between Kings College London and The Typing Works.

Following publication of the primary paper, anonymised electronic REDCap data will be exported and stored alongside anonymised transcriptions of interviews indefinitely on the King's Open Research Data System (<https://www.kcl.ac.uk/researchsupport/managing/preserve>), with proof of ethical approval as a condition of access.

## **13 Statistical considerations**

[name] will lead statistical aspects of the study design and analyses, including supervision of the trial statistician (to be appointed).

### ***13.1 Sample size***

Participants: The recruitment target aims to have a sufficient number of participants to provide the operational experience to plan a definitive trial; provide reasonably robust estimates of our feasibility outcomes; and to estimate the variability of the proposed patient-reported outcomes to inform a future sample size calculation. A recruitment target of 60 participants (30 per treatment arm) will allow overall retention rate at 12 weeks to be estimated with precision of  $\pm 11\%$ , using an exact 95% confidence interval, based on previously observed retention rates of  $\sim 80\%$  for the same

population in the community setting. Assuming a non-differential retention rate of 80% at 12 weeks follow-up, this target will provide follow-up outcome data on ~24 participants per group.

Professionals: Target recruitment is 80% of therapists involved in intervention delivery and invites extended to service managers from each site. This is estimated to be 12 therapists and 4 managers across sites.

## **13.2 Statistical analysis**

### Quantitative data

A statistical analysis plan will be finalised ahead of database locking and reporting will follow the CONSORT guidance for pilot and feasibility studies. Primary (descriptive only) analyses will follow the principles of intention to treat.

A CONSORT flow diagram will display data from screening, recruitment and follow-up logs enabling estimation of eligibility, recruitment, consent and follow-up rates. Confidence intervals for recruitment and retention rates will be produced to inform assumptions for planning the definitive trial. Completion rates will be estimated for outcome measures at each time-point, including resource use data. Participants' baseline characteristics will be summarised by allocated group with descriptive statistics (measures of central tendency and dispersion). Patient-reported outcomes, and acceptability will be summarised by allocated group at each follow-up, with descriptive statistics (measures of central tendency and dispersion). Between-group differences, including in changes from baseline, will be reported for the patient-reported outcomes with corresponding confidence intervals.

For patients who do not speak English, the count of pseudo-anonymised patient-reported outcome measures circulated and returned by post will be documented. The content of the patient-reported outcome measure will be described narratively ensuring participant anonymity is preserved (the language versions circulated will not be specified in reporting).

The quantitative analysis will be completed by a trial statistician using well-validated statistical packages after database lock at trial end. A TSDMC will monitor screening and recruitment rates, accruing outcome data and safety reporting. There are no interim analyses planned.

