## **9.3 Randomisation Procedures**

Participants will be allocated in 1:1 ratio to intervention or control groups. The Exeter Clinical Trials Unit (ExeCTU) will generate the random allocation sequence, stratified by recruiting site, with minimisation (with random element) for pre-fracture mobility (freely mobile outdoors without aids, mobile outdoors with one aid, mobility outdoors with two aids or frame).

Randomisation of a participant will take place after baseline data collection is completed following discharge from hospital, using a secure internet-based system, developed and maintained by ExeCTU

to ensure allocation concealment. Treatment allocation will be linked to a participant identification number (PID) and the clinical team will be notified. Group allocation will be documented in the patient's medical notes and on an enrolment log.

There are no anticipated circumstances under which the randomisation codes may need to be broken.

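### The pre-fracture mobility variable defined for baseline comparison cannot be mapped to the levels used for minimisation; as a lesser point, a baseline-adjusted contrast would serve the sample-size aim better than the change score that is named

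*Protocol*

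**What the plan says.** **Allocation.** Protocol section 9.3: "Participants will be allocated in 1:1 ratio to intervention or control groups". The sequence is "stratified by recruiting site". Balance on a second factor is sought by "minimisation (with random element) for pre-fracture mobility (freely mobile outdoors without aids, mobile outdoors with one aid, mobility outdoors with two aids or frame"). Allocation comes only once baseline data are in.

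**Baseline variable.** Section 12.1 lists the characteristics used to compare the allocated groups. Among them is "prefracture mobility (independent, with aid, with support of 1 person"). Table 1 (section 21.4) has a single categorical mobility item, marked pre-fracture, collected at baseline by interview. Its levels are not given.

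**Analysis.** Section 13.2: "Primary (descriptive only) analyses will follow the principles of intention to treat", and "Between-group differences, including in changes from baseline, will be reported for the patient-reported outcomes with corresponding confidence intervals". No model or covariate is named. The same section says "A statistical analysis plan will be finalised ahead of database locking".

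**Size and purpose.** Section 13.1: "A recruitment target of 60 participants (30 per treatment arm"), with 80% retention at 12 weeks giving about 24 per group. One stated purpose is to estimate outcome variability for a later sample size calculation, and section 6.3 lists an indicative sample size as an objective.

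**The concern.** The protocol fixes two definitions of what should be one variable, and they disagree. This cannot be left to the statistical analysis plan, because it affects the case report form and the randomisation entry, both of which come before any analysis. A baseline table built from the section 12.1 item would not show whether minimisation balanced the arms on its own factor. An analyst wishing to adjust for that factor could not do so from the item. Staff collecting the item would not have the answer that minimisation needs.

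The second question is whether the contrast named in section 13.2 suits its purpose. A change score uses the baseline value less efficiently than regression on baseline does. The residual SD and the baseline correlation are the quantities that a baseline-adjusted definitive trial would be sized on.

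**Working it through.** **1. The two codings side by side**

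| Section 12.1 level | Section 9.3 level it could correspond to |
|---|---|
| Independent | Probably no aids, but section 12.1 does not specify outdoors |
| With aid | One aid, or two aids or a frame: cannot be separated |
| Support of one person | None; aid use is not recorded |

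Only the first row gives a plausible one-to-one match, and that is by inference. In the second row two of the three minimisation levels collapse into one. In the third row, a participant helped by another person may have used any number of aids, and the item does not say which.

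Such participants are not ruled out on paper. The exclusion in section 8.2 concerns people likely to need two or more persons to support mobility on discharge. Table 1 lists no second mobility item from which the missing detail could be recovered.

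**2. The protocol's own figures**

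- Follow-up numbers: 30 × 0.80 = 24 per arm, as stated.
- Retention precision: 80% of 60 is 48. The exact (Clopper-Pearson) 95% interval for 48/60 is 67.7% to 89.2%, a half-width of 10.8 points, which agrees with the stated ±11%.

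Both reproduce.

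**3. Size of the secondary point**

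Inputs: 24 per arm (section 13.1), and equal SDs at baseline and follow-up (assumed). The baseline-to-follow-up correlation r is also assumed, because the documents give neither an SD nor a correlation. Half-widths are in units of the outcome SD:

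- Follow-up values only: t(46) × √(2/24) = 2.013 × 0.2887 = 0.581
- Change from baseline: 0.581 × √(2(1 − r))
- Baseline-adjusted: t(45) × √(2/24) × √(1 − r²) = 2.014 × 0.2887 × √(1 − r²)

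| r (assumed) | Follow-up only | Change | Adjusted | Adjusted/change variance, (1 + r)/2 |
|---|---|---|---|---|
| 0.3 | 0.581 | 0.688 | 0.555 | 0.65 |
| 0.5 | 0.581 | 0.581 | 0.504 | 0.75 |
| 0.7 | 0.581 | 0.450 | 0.415 | 0.85 |
| 0.8 | 0.581 | 0.368 | 0.349 | 0.90 |

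The adjusted interval is narrower than the change-score interval by 1 − 0.555/0.688 = 19% at r = 0.3 and by 1 − 0.349/0.368 = 5% at r = 0.8.

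Site and mobility terms use further degrees of freedom. With two for mobility and three for site (four sites assumed), the quantile becomes t(40) = 2.021. At r = 0.5 the half-width is then 2.021 × 0.2887 × 0.866 = 0.505, so the cost in the quantile is negligible. Any gain from the site and mobility terms themselves cannot be computed from the documents.

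**The case against.** A reader might infer from section 13.2 that the contrasts will ignore baseline, site and the minimisation factor, and that the resulting intervals are therefore wrong. The documents do not support that. The sentence names no model, does not call the differences unadjusted and excludes no covariate. A change score does use the baseline value. Choosing covariates for descriptive estimates is ordinary content for the statistical analysis plan, which the protocol promises and which is not at hand. No progression criterion in Figure 3 depends on a treatment difference, so no decision rests on the width of these intervals.

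It would also go too far to say that the planned analysis denies the definitive trial its inputs. The outcomes are collected at baseline and at each follow-up, so r can be computed directly. It can also be recovered from the three SDs as r = (s₀² + s₁² − s_Δ²)/(2·s₀·s₁). What stands is that reporting r and the residual SD is not promised.

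On mobility, the best defence is that minimisation cannot run unless each participant's level is entered, so the randomisation system must hold it. The same trials unit builds that system and the trial database. This is a good reason to think the information will exist, and it rules out any claim that it is lost. It does not remove the contradiction: the protocol does not say that the stored level reaches the analysis dataset, and section 12.1 names a differently coded variable for comparing the groups. Table 1 gives no levels, so it neither causes nor resolves the mismatch.

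**Conclusion.** The mobility mismatch is established on the text of sections 9.3 and 12.1 and needs no assumption. As defined, the baseline variable cannot provide the minimisation level, demonstrate balance on it or serve as the covariate. The practical harm is limited because the level used must exist in the randomisation system.

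The analysis point is a recommendation and does not identify an error. Baseline adjustment would narrow the interval by about 19% to 5% relative to the change score over assumed correlations of 0.3 to 0.8. At 0.5 the half-width would be about 0.50 SD, against 0.58 SD for both the follow-up-only and change contrasts. These sizes rest on equal SDs, 24 per arm and correlations that the documents do not supply. No stated sample size or precision figure changes.

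**What to change.** 1. Use the three minimisation levels of section 9.3 in section 12.1 and Table 1, and record support from another person as a separate item. Alternatively, state that the level recorded at randomisation is exported and is the analysis variable. The cost is a wording change and one recoded form item, or one exported field.

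2. In the statistical analysis plan, report the between-group difference at each follow-up from a linear model of the follow-up score on arm, baseline score, site and minimisation level, with a 95% confidence interval and no test. Report the residual SD and the baseline correlation alongside it. The change-score difference can remain as a supplementary description. Once item 1 is settled this needs no new data, only a few degrees of freedom for site and mobility.
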